### Randomization

On a first phase, professionals of the HCP in Lleida are informed of the purpose and the methodology of the study and are invited to participate in it. Sixteen HCPs accepted to cooperate in this study. Each HPU is responsible for the recruitment of participants and for the checking of their eligibility. Randomization will be centralized at the Primary Care Research Institute (IDIAP) Jordi Gol in Lleida. Each cooperating healthcare paediatric unit (HPU) will provide a random list of their patients/children fulfilling age and BMI SD scores inclusion criteria according to the data from their health clinical records. These eligible children will be randomly assigned to one of the study groups. Randomization will insure that patients are distributed to the 2 groups homogenously in terms of age and gender. Group homogeneity with regard to age will be assured by stratified randomization according to the age group: 6,7,8,9,10,11,12 years old (7 groups) in each HPU (16 HPU).

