### Recruitment strategy

Next, each HPU will phone/contact eligible families and will invite them to participate in the study. At that point participants will be informed about their study/case group. HPUs will recruit participants consecutively and on an alternate list mode basis, i.e. once they have recruited one eligible child from the intervention group list, they move on to recruit another participant from the CG list. Families of eligible children that accept to participate will be referred to their healthcare paediatric unit office for anin-depth explanation, followed by a medical assessment (basic exploration and blood test to check for inclusion and exclusion criteria). Children’s assent and written parental informed consent will be obtained from children who fulfil the inclusion criteria and with no exclusion criteria. The family will be finally included in the study.

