### Ethical aspects/Considerations

The study will be carried out according to the principles of the “Declaration of Helsinki” and subsequent revisions [25] and to the Guidelines for Good Practice in Primary Care Research of the IDIAP [26]. This protocol has been approved by the Clinical Research Ethics Committee (CEIC) of the Primary Care Research Institute (IDIAP) Jordi Gol. The study methods are in agreement with the CONSORT guidelines for reporting randomizated trials [27].

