#### Measurements

As the intervention is principally focused on a family-based behavioural multi-component intervention for children’s obesity, both children and parents will be assessed. The main measure parameters are described in Table 3.

**Table 3 T3:** Measurements

**Aim**		**Nereu and Counselling group measures**	
		**Children**	**Parents**
Cardiovascular risks factors	Anthropometry	Weight	Weight and Height
		Height	
		BMI z score	
		Waist circumference	
		Waist-size index	
		Triceps skinfold	
		Subscapular skinfold	
	Blood pressure	Diastolic and systolic pressure	NOT analysed
	Blood test	Cholesterol (LDL, HDL), triglycerides, glucose, insulin, TSH and cortisol ^1^	NOT analysed
Physical condition	Physical condition	ALPHA test set [42]	
Behaviours	Physical activity	Seven-days Accelerometry	International Physical Activity Questionnaire IPAQ [74]
		Seven days recall physical activity questionnaire (PAQ-C) [46]	
	Nutrition	24 h dietary recall (x 3 days)	Frequency consumption (CFCA –adults version)
		Frequency consumption (CFCA – children version)	
Psychological aspects	Physiological, physical and cognitive	Physical activity self-efficacy [64]	Health-specific self-efficacy [82]
		Physical self-concept (MIFA) [66]	
		Body-image: Figure Rating Scale [67]	
		Physical activity enjoyment (PACES) [69]	
Health related quality of life	HRQOL	PedsQL 4.0 [70]	
Health economic data	Cost-effectiveness	CHU 9D [73]	EQ-5D EuroQol Group [84]
Modifiers variable	Pubertal maturity	Tanner pubertal stage [88]	
	Socio-economical and demographic parameters	Some questions from de National Healthy Survey for children [89] and for parents [90]	
	Adherence	Attendance log	
	Satisfaction	Survey	

^1^the measurement will be undertaken 2 times: at baseline and at the end of the intervention.

Measurements will be assessed before and at the end of the intervention, and 6 and 12 months after the end of it.

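### Written parental consent and the child's assent come after the eligibility examination and blood test, and only for children who pass them

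*Protocol article*

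**What the plan says.** The sequence is spread over two sections of the protocol article.

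- **Randomization.** Each unit lists children "fulfilling age and BMI SD scores inclusion criteria according to the data from their health clinical records". The next step described is allocation: "These eligible children will be randomly assigned to one of the study groups". Both steps use existing records and involve no procedure on the child.
- **Recruitment strategy.** The unit contacts the family, tells them the allocated group and invites them. "Families of eligible children that accept to participate will be referred to their healthcare paediatric unit office" for a detailed explanation, "followed by a medical assessment (basic exploration and blood test to check for inclusion and exclusion criteria").
- **Recruitment strategy, next sentences.** The child's "assent and written parental informed consent will be obtained from children who fulfil the inclusion criteria and with no exclusion criteria". Then: "The family will be finally included in the study".

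The Blood tests section says that study blood is taken by venipuncture after an overnight fast and analysed at a hospital laboratory. A footnote to Table 3 in the Measurements section says of the blood test that "the measurement will be undertaken 2 times: at baseline and at the end of the intervention". The Ethical aspects section makes a general ethical commitment and reports ethics committee approval.

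**The concern.** The children are 6 to 12 years old, and the blood test is the one measurement in Table 3 that breaks the skin. The only purpose given for the screening test is to check trial eligibility, and the visit takes place because the family was invited into the trial. On the protocol's description it is therefore a study procedure, and it comes before written parental permission and the child's assent.

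What is at stake is participant protection at an invasive step. A unit that follows the text literally draws blood with no documented consent. For a child who then proves ineligible, the text provides for no consent at any time. The primary outcome (BMI SD score), the power and the planned analysis are not affected.

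**Working it through.** No arithmetic is needed to establish the order. The check is whether the text fixes it, and whether any other part of the protocol changes it.

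**1. Order as written (Randomization and Recruitment strategy)**

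| Step | Event | Agreement documented by then |
|---|---|---|
| 1 | Pre-selection from clinical records | None needed for a procedure |
| 2 | Random assignment | None |
| 3 | Contact, group disclosed, family accepts | Oral acceptance |
| 4 | Detailed explanation at the unit | Oral acceptance |
| 5 | Examination and blood test for eligibility | Oral acceptance |
| 6 | Child's assent and written parental consent, from eligible children | Written |
| 7 | Final inclusion | Written |

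**2. Is this only loose sentence order?** No. Step 6 is restricted to children who fulfil the inclusion criteria and have no exclusion criterion. Step 5 is the means of finding that out. Step 6 therefore needs the result of step 5 and cannot come before it without changing the text.

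**3. Is an earlier or separate consent described elsewhere?** The Ethical aspects, Blood tests, Statistical methods, Possible risks and burdens, and Discussion sections were checked. None describes consent to screening.

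**4. Who is affected?** Let *s* be the number of children who attend and fail screening, and *r* the number who pass but whose family then declines. The number tested before documented consent is

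included + *s* + *r* = at least 100 + *s* + *r*.

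The 100 is the recruitment target in the Sample size section. The article gives neither *s* nor *r*, so 100 is a lower bound at full recruitment. The *s* children are never asked for written consent. Children who are randomised but whose families decline at the first contact are not counted, because they have no test.

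**5. Does the timing of allocation matter?** No. If random assignment were moved to after step 7, steps 3 to 6 would keep the same order and the problem would remain.

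**The case against.** Several parts of the opposing case stand and limit the point.

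- **Families have agreed to something.** Only those who accept come to the unit, and they receive an explanation before the test. A reader might infer that nobody has consented in any sense. The text does not support that: what is absent at the time of the test is written parental consent and the child's assent.
- **The test may overlap with care.** It is done at the child's own unit, and the Abstract describes children referred by their paediatricians because of their weight. The exclusions include thyroid and adrenal disease. The article gives only the eligibility purpose and never calls the test routine, but it does not rule out overlap.
- **Ethical aspects section.** A reader might infer a direct contradiction with the statement that "The study will be carried out according to the principles of the" Declaration of Helsinki. That section sets no rule on when consent is taken, so a contradiction cannot be shown from the document. Nor does the reported committee approval alter the written order.
- **Baseline blood outcomes.** A reader might infer that the baseline values rest on blood taken before consent, or else that at least 100 children have an avoidable second draw. Neither follows. The article never says that the screening sample is the baseline sample. It gives no fasting rule, analytes or laboratory for screening, whereas the study samples are fasting and go to a hospital laboratory, and the Trial design section places all measurements at one research unit.
- **Screen-failure results.** Nothing in the document supports a claim that these could not be kept or reported.

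It may also be said that a journal article condenses its protocol. That excuses omissions, but here the article states a sequence, and the sequence is what needs correcting.

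**Conclusion.** The point holds in a limited form. The Recruitment strategy section places written parental consent and the child's assent after the eligibility examination and blood test, and restricts them to children who pass. Each child whose family accepts orally and attends is tested for a study purpose before any documented consent, and screen failures never reach the consent step. At full recruitment that is at least 100 children plus an unstated number of others.

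This rests on two assumptions: that the test is a study procedure, as its only stated purpose implies, and that no separate screening consent exists outside the article. If either is wrong, the section still needs a sentence saying so. No conclusion is drawn about the validity of the baseline blood data.

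**What to change.** In the Recruitment strategy section:

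1. Obtain written parental consent and the child's assent at the end of the detailed explanation, before the medical assessment and blood test.
2. Make final inclusion conditional on the result of that assessment.
3. If the blood test is part of routine care, or a separate screening consent is used, state this.
4. State whether the screening sample is also the baseline sample for the blood outcomes. One sample need not serve both purposes, since the article does not show that fasting, analytes and laboratory match.

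The cost is two steps exchanged within the visit and a wording amendment. The small downside is that some children will have consented and then fail screening; they should be counted in the flow diagram.

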### Sample size

The aim of the research team is to recruit 50 subjects per group, computing a total of at least 100 participants. The calculation of the sample size takes as its primary outcome intervention efficacy - the reduction of BMI SD scores after the intervention, as specified in a published meta-analytic review of trials [24]. The sample size was calculated in order to detect one BMI SD scores reduction (effect size = 0.60 [24]), according an 80.0% statistical power, 5% significance level to detect differences between groups with two independent samples. It is assumed a 20% dropout rate was estimated.

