#### Possible risks and burdens

This is a long term intervention that requires children and parental attendance tothe scheduled sessions as well as to the assessment appointments for the evaluation of the short, medium and long term effects. The risk of abandonment is high but we will try to reduce it by providing constant feedback to participants and their families.

On the other hand, our previous experience shows that the potential physical risks in the study are minimal. Further, the physical sessions for children have been designed and chosen especially for them. Attention has been put on enjoyment and on lack of excessively (physical and psychological) challenging situations, as well as on trying to minimize the risk of injury, even if this cannot be eliminated completely. Moreover, sessions have been scheduled to avoid overloading children. In the case that of one of these situations happens, the child will immediately be derived to their paediatrician or specialist.

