## Discussion

To the authors’ knowledge, this is the first intensive family-based behavioural multi-component intervention for childhood obesity management led from the healthcare paediatrician with a longitudinal design in Spain. It targets the same principal contents for both parents and children in the easiest manner for each age group, focusing on their posterior application in their home unit. The study aims to establish a long-term healthy behaviour related to achieving a healthy weight status, physical activity and eating behaviour in order to improve their quality of life and reduce possible health problems. The study design is a randomized controlled multicenter clinical trial using two types of treatment (Nereu and Counseling) with follow-up measurements at 9, 15 and 21 months after the intervention. We believe that our study is in agreement with the principal recommendations, mentioned by Oude Luttikhuis [17], where it is recommended for family interventions to combine diet, physical activity and behavioural components focused on behavioural changes with good methodological interaction and assessing the effects in a long term period [7]. In addition, the present study has a longitudinal design with a long-term follow-up, and as it is well known, it makes it possible to gather a higher level of evidence than a cross-sectional analysis.

Following the previous editions of the Nereu program, we expect a low drop-out and the probable drop-out rate/percentage has been contemplated in the sample size. However, if we have a high drop-out and we do not achieve the sample provided, it could occur that, the outcome variables do not become statistically significant due to the lack of statistical power. However, we must take into account that paediatricians use the Healthy Child Programme which computerizes medical records of all children, and also during the recruitment period paediatricians can look for a higher sample of children if required. In the recruitment period contamination between groups could occur, as children are randomized from the same healthcare centre or district. We are going to try to prevent this by doing the NP in an external school facility and the assessment periods will be undertaken on different days.

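### Fifty children per group does not give 80% power at effect size 0.60 with 20% dropout (about 75%), and the one-unit target matches 0.60 only with an unstated SD of about 1.67

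*Protocol article*

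**What the plan says.** The protocol article's Sample size section fixes the recruitment target: "The aim of the research team is to recruit 50 subjects per group, computing a total of at least 100 participants". It names the reduction in BMI SD score as the primary outcome and gives the basis of the calculation: "The sample size was calculated in order to detect one BMI SD scores reduction (effect size = 0.60 [24]), according an 80.0% statistical power". The significance level is 5%, for a comparison of two independent samples. On losses it says: "It is assumed a 20% dropout rate was estimated".

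The Discussion confirms that the 50 is meant to include the dropout allowance: "we expect a low drop-out and the probable drop-out rate/percentage has been contemplated in the sample size". The section on possible risks and burdens is less optimistic about retention: "The risk of abandonment is high but we will try to reduce it".

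The article does not state the SD of the BMI SD score or of its change, or whether the test is one-sided or two-sided.

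**The concern.** Effect size, power, significance level, dropout and group size are all given, so the calculation can be checked once the sidedness is assumed. On the two-sided reading, the number per group is too small for the power claimed.

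The target effect is also expressed in two ways within one sentence, as a raw difference of one BMI SD score and as an effect size of 0.60. These describe the same target only for one particular SD, which the article does not give.

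This is the trial's only justification of its size, and it concerns the primary outcome. If the stated power is not the actual power, and the reader cannot tell which difference the trial was built to detect, a null result cannot be judged against the stated target.

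**Working it through.** **Inputs.** From the Sample size section: d = 0.60, power 80%, alpha 5%, two independent samples, dropout 20%, 50 per group. From the Discussion: dropout is already in that number. Assumptions made here: 0.60 is a standardised difference (difference divided by SD), and the test is two-sided. A one-sided test is also tried.

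**1. Attempt to reproduce the 50.** Completers per group by the normal formula:

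n = 2(z₀.₉₇₅ + z₀.₈₀)² / d² = 2(1.960 + 0.8416)² / 0.36 = 43.6, so 44.

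The exact (noncentral) t calculation gives 44.6, so 45. Recruitment allowing for dropout is n / (1 − 0.20):

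| Reading | Completers per group | To recruit per group |
|---|---|---|
| Two-sided, n / 0.8 | 44 (normal), 45 (t) | 55, 57 |
| Two-sided, n × 1.2 (an incorrect but common inflation) | 44, 45 | 53, 54 |
| Two-sided, no dropout allowance | 44, 45 | 44, 45 |
| One-sided, n / 0.8 | 35, 36 | 44, 45 |
| d = 1.0, two-sided, n / 0.8 | 16, 17 | 20, 22 |

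None of these gives 50.

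**2. Power that 50 per group delivers.** Completers: 50 × 0.80 = 40 per group.

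Normal approximation: Φ(0.60 × √(40/2) − 1.960) = Φ(2.683 − 1.960) = Φ(0.723) = 76.5%. The t calculation gives 75.5%.

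Effect detectable with 80% power at 40 per group: (1.960 + 0.8416) × √(2/40) = 0.626 by the normal formula, and 0.634 by the t calculation.

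**3. Dropout that 50 per group can absorb.** 1 − 45/50 = 10% (t), or 1 − 44/50 = 12% (normal). With no dropout at all, 50 per group gives 84.4% (t).

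**4. The two statements of the target.** Effect size = difference / SD, so 0.60 = 1 / SD and SD = 1 / 0.60 = 1.67 BMI SD-score units. If the SD were 1 instead, a one-unit difference would be d = 1.0. That needs 2(2.8016)² = 15.7, so 16 completers per group (17 by t), and 40 completers would give about 99% power. The two readings therefore differ from about 17 to about 45 completers per group.

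**The case against.** Four points can be made for the plan.

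First, the total is a floor of 100, and the Discussion says paediatricians could look for more children if needed and warns that high dropout would cost power. This limits the practical consequence. It does not make 50 the right planned number, because on the stated inputs the floor itself should be 110 to 114 in total, and the loss of power occurs at the planned dropout, not only at a higher one.

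Second, the shortfall depends on reading 0.60 as a standardised difference and the test as two-sided. That stands as a condition. One-sided, 40 completers would have about 84.5% power, and a one-unit difference with SD 1 would be amply powered. But neither reading yields 50, and the article states neither a one-sided test nor an SD of 1.

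Third, a baseline-adjusted analysis could recover some power. The calculation stated is for two independent samples, however, and the article gives no correlation on which to base an adjusted figure.

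Fourth, on the scale of the target, a reader might infer that one BMI SD score cannot be an effect size of 0.60. The documents do not support that: the two agree at an SD of 1.67. A standard deviation score has SD 1 in its reference population, and these children are selected for overweight or obesity, so 1.67 looks large. No SD is given for this sample, though, so it is not ruled out. Nor do the documents show which of the two targets was intended, so it would be wrong to treat the one-unit figure as the slip and strike it out.

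The differing remarks on expected dropout do not change the sums, since neither gives a rate other than the 20%.

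**Conclusion.** The point holds. On the plan's own inputs, with a two-sided test and 0.60 taken as a standardised difference, 50 per group falls 5 to 7 children per group short. Power is about 75%, against the 80% stated. The gap is modest: about 4 to 5 percentage points, or a detectable effect of 0.63 in place of 0.60. It is not rounding, since the stated number suits a dropout of about 10%, half the rate assumed.

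The equation of one BMI SD score with 0.60 is unsupported rather than impossible. It needs an SD of about 1.67 that is neither stated nor justified. Until that is settled, the difference the trial was sized to detect is unclear.

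**What to change.** Keep the 100 children and correct the Sample size section:

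- State that 50 per group, leaving 40 completers per group after 20% dropout, gives about 75% power for a standardised difference of 0.60 (two-sided 5%), and 80% power for about 0.63.
- Reconcile the two targets: give the raw difference in BMI SD-score units, the SD assumed, whether it is the SD of the change or of the follow-up value, and the source of each.
- State the sidedness of the test. If the reconciled target or the sidedness differs from d = 0.60 two-sided, recompute the power from the new inputs.

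This changes wording only; no extra recruitment is required. The cost is a slightly less favourable stated power.

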### Ethical aspects/Considerations

The study will be carried out according to the principles of the “Declaration of Helsinki” and subsequent revisions [25] and to the Guidelines for Good Practice in Primary Care Research of the IDIAP [26]. This protocol has been approved by the Clinical Research Ethics Committee (CEIC) of the Primary Care Research Institute (IDIAP) Jordi Gol. The study methods are in agreement with the CONSORT guidelines for reporting randomizated trials [27].

### Intervention

#### Nereu programme

The NP is an 8-month intensive family-based behavioural multi-component intervention (from October to May, that is, an academic year), consisting of 4 components (Table 1): (a) physical activity sessions for children, (b) family theoretical and practical sessions for parents, (c) behaviour strategy sessions, that involve both parental and child participation and (d) weekend extra activities.

**Table 1 T1:** Contents of the assembly of children, the family theoretical counseling sessions for parents and the behavior strategies sessions for both

**Target/term**	**Parents/children**			**Parents’ sessions contents**	**Children’s assembly contents**
	**Phase**	**N**	**Behavior change strategy**		
**1st Term (October-December) Getting informed**	Concienciation (**Attention**)	1	Explaining expectations	Presenting the programme	What is Nereu Programme?
			Information on health components of the programme	Understanding the expectations of the parents at the beginning of the Nereu Programme	What do you want to know?
		2	Information about healthy food	Reflecting on the current diet and healthy food benefits	Benefits of healthy food
			Barrier identification		
		3	Information on outcomes	Making them aware of the importance of PA	Why should we take part in sport?
		4	Provide information about healthier diet	Knowing the behaviours and actions that help us improve our diet	Let's go to eat healthy and funny!
		5	Provide information about healthier behaviour	Becoming familiar with their lifestyle and how to make it more active	How can I go to the school?
		6	Explaining how the programme aims to encourage healthier lifestyles	Setting short-term goals (behaviour strategy session I)	
**2nd Term (January-March) Becoming aware**	Modelation (**Retention**)	7	Instructions about nutrition	Understanding and knowing eat quantities	The traffic light game
		8	Ways in which they can achieve a more active lifestyle/Identifying barriers to participation	Becoming familiar with their availability and requirements in order to be more PA. What we should be doing!	Family photography!! Which sport will you Take part in?
			Self-monitoring of existing PA		
		9	Provide information about healthier eating	Myths related to nutrition	What do we know about nutrition?
		10	Encouraging healthier lifestyle	Using different tools to become more active	The weather is good, let’s go and have fun!!
		11	Overcome specific barriers	Giving options to eat on specific days (Christmas, restaurants…)	Ticket-aaaa!!! Eating out side!!
		12	Social support and change	Behaviour modification strategies day-to-day	Where are we going next weekend?
		13	Provide instructions about healthier food	knowledge about how to interpret advertising and how buy food	Let’s go to buy!
		14	Provide feedback on performance	Ways in which they can incorporate PA into their lifestyle.	Why do we use the elevator?
		15	Encouragement and setting goals on PA and nutrition	Setting medium-term goals (behaviour strategy session II)	
			Maintaining behaviour strategies		
**3rd Term (April-Mai) Committing and keeping up**	Autonomy (**Reproduction**)	16	Provide knowledge about healthier eating	Learning to make a balanced menu	How do a balanced menu?
		17	Specific encouragement	Relation between PA and food intake	Burning sweets!
			Decisional balance		
	Evaluation (**Motivation**)	18	Self PA evaluation	Evaluating the implementation of PA	How active are we?
		19	Self-Diet evaluation	Evaluating the implementation of Diet	How well you eat?
		20	Encouraging PA and nutrition	Keeping up medium and long-term behaviour (behaviour strategy session III)	
			Maintenance behaviour strategies		
	Closure	21	Enjoying a healthy day together	Closing Party	
**1 each term**	3 weekend extra activities	--	Encouraging active behaviour in an experiential manner and social support	3 extra family physical activities: Ski, FC Barcelona, Aqua party	

The whole intervention will take place in 3 different school centres and health care centres, which have been recruited especially for the intervention and with a strategic localization around the city, in order to facilitate their accessibility. The children’s physical activity sessions will take place using the sport equipments of the school, the theoretical sessions for parents at the same school or at the health care centre next to the school, and the behaviour strategy sessions will be performed in both places. Parents’ and children’s sessions will be performed simultaneously in order to facilitate their attendance. All intervention groups will have a maximum of 15 children and parents.

The 4 structured components are:

a). Physical activity sessions for children

The physical exercise programme offered to children will consist of 90 sessions (3 sessions per week, each lasting 60 minutes). The main aim of the sessions is to enhance a physical active behaviour, to look for greater enjoyment during physical activity tasks and meet and practise new sports and games in order to keep practising them for a long time.

All sessions are planned to be performed in a friendly uncompetitive atmosphere and adapted to the participants’ needs, because motivating and encouraging obese children to be physically active cannot be achieved following the same approach as for normal weight children [28]. Obese children are physiologically different from those who are normal weight, and they also have significant emotional differences [29]. In that sense, the sessions have been planned by specialists with at least 4 years of experience in physical activity with overweight and obese children and following the physical activity guidelines for children [30-32]. All the sessions will be performed by two coaches who have the sport science degree with specific knowledge and experience in sport treatment for children with overweight and obesity and who have also attended the specific Nereu course. The Nereu course has been addressed specially to teach and help coaches, nurses and physical activity professionals before starting with the intervention, with specific contents about obesity management.

All physical activity sessions have a similar structure but differ in their contents. Sessions have a four-part structure: assembly, warm-up, workout and cool down periods. During the assembly, the coach explains the day’s training task, attempts to motivate children and introduces contents related to health behaviour based on behaviour change strategies. The assembly’s contents (Table 1) are the same as the family theoretical and practical sessions’ contents for parents, but taught in a playful and experimental atmosphere. Teaching the same health behaviour contents and on the same day and at the same time to both parents and children looks for an improvement in the effectiveness of these contents and their application at home by the family unit. Afterwards, during the warm-up part, dynamic activities such as walking or jogging will be performed at low intensities looking for their activation before the main part. The main part of the session (workout) is primarily focused on being physically active, but as overweight and obese children generally are not especially fit and tend both to be sedentary and tend to have had poor experiences with sport [33], exercises will be planned in short periods of duration such as 4–5 minutes of moderate-high intensity activities intersected by periods of low intensity. Short bouts of intermittent exercise are considered most appropriate for this population [34]. The sessions are also designed looking for their enjoyment through practising and learning different kinds of sports, activities and abilities. Training tasks will be mainly aerobic, but strength, joint mobility and balance will be also included (Table 2). These have been planned according to 3 essential pillars: playing, enjoying oneself and moving in order for children to get rid gradually of their fear and reluctance to sports. The cool-down period is comprised by recovery exercises and static stretching allowing participants to recover.

In addition, each session from the workout part has been planned to be a moderate-high intensity activity. In that sense, one session every two weeks in each centre will be recorded by an accelerometer and heart rate monitor and followed with an assessment in order to be sure that children from the 3 PA centres follow and reach the same indications in terms of intensity.

b). Family theoretical and practical sessions for parents

The family programme consists of 21 theoretical and practical counselling sessions with a duration of 60 minutes each. The sessions will be in group and will take place once a week atthe same time as their children’s sessions, giving the family the opportunity to exchange experiences and establish shared compromises later at home.

The sessions will be carried out by trained nurses and physical activity education professionals skilled inmultidisciplinary behaviour including physical activity, nutrition and healthy behaviours (Table 1).

The overall focus of the parental sessions is to help families to make better healthy behaviour choices mainly in terms of physical activity and nutrition inside the family unit.

c). Behaviour strategy sessions, involving children and parents

The three behaviour strategies sessions for parents and children, one each term, have been planned to reinforce the acquisition of healthier physical activity and eating habits within the family in a more experimental and practical manner (Table 1).

The contents of the family theoretical and practical sessions, the behaviour strategies sessions as well as the assembly of physical activity sessions, are planned mainly according to the Social Cognitive Theory (SCT) of Bandura [35], and the guidelines of several institutions [32,36-38].

d). Weekend extra activities

Additionally, three extra weekend family physical activities (e.g. ski or water party) will be organized, one each term following the school calendar, in order to encourage and achieve this more active behaviour in an experiential way (Table 1). Participants’ friends or relatives will be also invited to take part in the activities, looking for their social and familial support. At the same time, plans are in place to help them to achieve the minimum recommendations of 60 minutes a day of moderate-vigorous physical activity [39].

**Table 2 T2:** Contents of physical activity training for children, family theoretical and practical sessions and behaviour change strategies

**Term**	**Children physical activity sessions**
**1st TERM (October-December) GETTING INFORMED**	Personal knowledge games
	Interaction group activities
	Collaboration games
	Traditional games
	Balance
**2nd TERM (January-March) BECOMING AWARE**	Different kinds of adapted sports without competition
	Games with alternative equipment
	Aerobic games
	Joint mobility
	Strength games
**3rd TERM (April-Mai) COMMITTING AND KEEPING UP**	Motor and physical abilities
	Aerobic tasks
	Strength exercise
	Different kinds of sports and activities
	Outdoor sports and games

